#### Procedure for unblinding if needed {17b}

In situations where an adverse event or complication has occurred such that reoperation or other invasive intervention is deemed necessary, it may be necessary to unmask the intervention allocation to plan appropriate treatment. Requests to unmask will be made electronically via the treating surgeon and logged within the study masterlist. Requests will be managed by the senior engineer with access to the allocation key.

### Data collection and management

#### Plans for assessment and collection of outcomes {18a}

Patient personal and medical data is routinely collected and stored in the participating surgeons’ practice management systems (Bluechip, MedicalDirector, Australia and Genie, Genie Solutions, Australia). Patient demographic data, comorbidities and full patient history relating to the history and onset of the foot and ankle condition will be recorded in the practice management system during patient consultation. Radiological reports collected routinely as part of diagnosis, surgical planning and postoperative follow-up, full description of diagnosis, mode of treatment and details of nonoperative and surgical interventions, and timing of treatments will also be recorded in the practice management system during patient consultation. Intraoperative data, patient-reported outcomes data and findings from clinical examination will be electronically entered into the SOFARI registry via web-based forms (Google Suite, Google, USA) by the clinical research nurse, research team, surgeon or the patient.

Intraoperative (surgical technique), patient-reported (FAOS-Pain) and clinical outcome (complications) data collected during this trial will additionally be linked to the SOFARI registry via the same modes of data entry. Data collection will continue until the minimum sample size requirements for the study are met with complete records established.

#### Plans to promote participant retention and complete follow-up {18b}

Once a participant is enrolled in the study, they will be contacted at 3, 6 and 12 months postoperatively for PROMs follow-up data collection as per the existing SOFARI registry procedures. The routine contact will facilitate participant retention up until the 12-month follow-up. Follow-up reminders will be administered from the clinic, and the electronic questionnaires can be completed remotely at the patient’s convenience. There is an additional opportunity to collect PROM data when the patient visits the clinic for their 12-month follow-up, if they have not completed the electronic forms.

In cases where the intervention protocol is not followed, the participant will be removed from the trial and the randomisation slot filled by the next participant recruited into the trial.

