#### Criteria for discontinuing or modifying allocated interventions {11b}

If the participant requests a particular intervention, they will be unenrolled from the trial, and their data will not be included in later analyses.

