#### Strategies to improve adherence to interventions {11c}

Adherence to the randomised intervention allocation will be assessed by comparing the patient osteotomy group allocation as identified in the operation report, to the trial master sheet with the allocation information. Follow-up and PROM compliance will be encouraged through follow-up reminders, as part of the SOFARI registry processes. The primary outcome will be collected electronically, with controls in place to prevent partial completion of the questionnaire.

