### Assignment of interventions: allocation

#### Sequence generation {16a}

Participants will be randomly assigned to receive either a flat-cut Weil osteotomy (control, group A) or wedge-cut osteotomy (experimental, group B) procedure using a central computer-based simple randomisation system, with a 1:1 allocation without blocking. The random allocation sequence will be embedded within the clinical registry via a randomisation algorithm (Matlab 2018b, Mathworks Inc., USA). The allocation will be communicated electronically to the treating surgeon via an allocation code comprising nondescript terminology, whereby the allocation cannot be inferred from the label to other study personnel.

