## Statistical methods

### Statistical methods for primary and secondary outcomes {20a}

#### Principles

An analyst blinded to treatment allocation will perform the primary and secondary analyses, by comparing the intervention group to the control group. Data will be analysed following intention-to-treat principles (i.e. participants will be analysed in the group to which they were randomised to). Data normality of baseline characteristics and process measures will be evaluated by visual inspection of histograms. Continuous variables will be presented as means and standard deviations for normally distributed variables: median, minimum, maximum and interquartile range for non-normally distributed variables. Frequencies and percentages will be used to summarise categorical variables. Percentages will be calculated using the number of participants for whom data are available as the denominator. Alpha will be set at 0.05 and effect sizes as described in the sample size calculation will be considered of interest.

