#### Data integrity

All data points for the study core dataset will be retrieved electronically, so comparing to original paper records will not be necessary. Data integrity will be defined in the context of this study as completeness, consistency and validity. An error rate of < 3% will be considered acceptable across the total of fields assessed.

Patients who are otherwise lost to follow-up will be included in the analysis under an intention-to-treat framework. Where appropriate, imputation will be used to provide estimates of outcomes for patients lost to follow-up. To mitigate the effects of loss to follow-up on the analysis, the sample size factored in an estimated dropout rate of 10% to ensure adequate power for analyses requiring listwise deletion of missing data.

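### Removing participants whose allocated technique was not followed, and refilling their randomisation slot, contradicts the stated intention-to-treat analysis and may weaken concealment

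*Protocol article*

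**What the plan says.** All references are to the protocol article.

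- **Analysis principle.** Under Statistical methods, Principles, the analysis is by intention to treat: "participants will be analysed in the group to which they were randomised to". Data integrity repeats this for missing follow-up: "Patients who are otherwise lost to follow-up will be included in the analysis under an intention-to-treat framework".
- **Removal and replacement.** Section {18b} provides that, after a departure from the allocated procedure, "the participant will be removed from the trial and the randomisation slot filled by the next participant recruited into the trial".
- **Participant requests.** Under {11b}, participants who ask for a particular technique are dropped: "they will be unenrolled from the trial, and their data will not be included in later analyses". No time limit is given.
- **Detection of non-adherence.** Under {11c} it is assessed by "comparing the patient osteotomy group allocation as identified in the operation report, to the trial master sheet with the allocation information".
- **Allocation.** Section {16a} describes allocation "using a central computer-based simple randomisation system, with a 1:1 allocation without blocking". Section {16b} withholds the code from the treating surgeon until the patient has been recruited, on the day of surgery.
- **Who knows and who recruits.** Section {17a} states that the treating surgeon cannot be blinded. Section {26a} has the participating surgeons discuss the study with patients and take consent.

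**The concern.** Departure from the allocated technique is the situation that an as-randomised analysis exists to handle. A rule that takes such patients out of the trial cannot be carried out together with a promise to analyse everyone as randomised. The patients who remain form a per-protocol set. The surgeon who knows the allocation also performs the operation, so membership of that set can depend on someone who is not blinded. If departures are related to prognosis and differ between arms, the comparison loses the protection of randomisation.

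The replacement half of the rule raises a separate question. Under simple randomisation no allocation depends on an earlier one. Passing a vacated slot to the next recruit creates such a dependence if the slot carries its arm with it. The next allocation could then be known before that patient consents.

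**Working it through.** The plan gives no figure on this point to reproduce. The check sets the sections side by side and then sizes the possible effect under stated assumptions.

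**1. Is the removal after randomisation?** The code is released on the day of surgery, once the patient is recruited ({16b}). Non-adherence is read from the operation report ({11c}), which exists only after surgery. Removal under {18b} on this basis is therefore after randomisation and normally after surgery.

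**2. Does another section resolve the conflict?** Data integrity keeps patients lost to follow-up in the analysis but does not mention patients removed for non-adherence. Section {20c} has protocol non-adherence in its heading, but its text deals only with missing data. The conflict stands.

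**3. What does slot reuse do to predictability?** Under simple 1:1 randomisation a guess at the next allocation is right 50% of the time. If the vacated slot keeps its arm, and the recruiting surgeon knows of the removal and recruits the next patient, it is right 100% of the time. With an assumed 5%, 10% or 15% of 80 patients removed, that would concern 4, 8 or 12 allocations. If a fresh draw is made, the figure stays at 50%.

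**4. How large could the bias be?** From the plan: target difference 15.3 / 2 = 7.65 points, SD 20.8, 80 patients, taken here as 40 per arm. Assumed: no true effect; the k patients with the worst prognosis in one arm are removed and replaced by k random patients; the correlation r between prognosis and outcome is 0.3 or 0.5; no covariate adjustment.

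Expected shift = (k / 40) × m × r × 20.8. Here m is the mean distance below average, in SD units, of the k lowest of 40 normal values: 1.69 for k = 4 and 1.51 for k = 6.

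| k | r | Formula | Shift (points) | Simulated shift |
|---|---|---|---|---|
| 4 | 0.3 | 0.10 × 1.69 × 0.3 × 20.8 | 1.05 | 1.05 |
| 4 | 0.5 | 0.10 × 1.69 × 0.5 × 20.8 | 1.76 | 1.74 |
| 6 | 0.3 | 0.15 × 1.51 × 0.3 × 20.8 | 1.41 | 1.42 |
| 6 | 0.5 | 0.15 × 1.51 × 0.5 × 20.8 | 2.36 | 2.35 |

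The simulations used 20,000 trials per setting. As a share of the target, the range is 1.05 / 7.65 = 14% to 2.35 / 7.65 = 31%. The two-sided rejection rate at a nominal 5% was 5.5% to 8.1%; repeat runs gave up to 8.4%.

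**5. A simpler cross-check.** If a share q of one arm is removed, and those patients would have scored D points worse than those kept, the shift is q × D. With q from 5% to 15% and D from 5 to 15.3 points (both assumed), it runs from 0.05 × 5 = 0.25 to 0.15 × 15.3 = 2.3 points, or 3% to 30% of the target.

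**6. Removals in both arms.** When the same worst-prognosis removal is applied to both arms, the expected shifts are equal and cancel. The simulated mean difference was then within 0.03 points of zero.

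**The case against.** The conflict between {18b} and the intention-to-treat statement has no good defence. The most that can be said is that the word otherwise in the Data integrity sentence hints at a deliberate carve-out for removed patients. Even then the analysis would not be intention to treat as the plan itself defines it.

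The objections to stronger readings do stand:

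- **Concealment.** A reader might infer that the rule certainly reveals the next allocation. The text does not say that a refilled slot keeps its arm; with a registry-embedded algorithm it could mean an enrolment place that receives a fresh draw. Even with reuse, the recruiting surgeon must know of the removal and recruit the next patient. There are several surgeons, the timing of the adherence check is not given, and {15} says all eligible patients will be approached.
- **Participant requests.** A reader might infer that {11b} also deletes patients after randomisation. No timing is stated. Participants are blinded and the code is released only on the day of surgery, so a request may well precede allocation. A later request from a blinded patient would not be driven by a known arm.
- **Type of analysis set.** The remaining set is per-protocol, not as-treated: nobody is moved to the technique received.
- **Direction and size of bias.** A reader might infer that the rule favours the wedge cut, because that arm has a second osteotomy. The documents give no non-adherence rate, reason or direction, and {25}, Provisions for post-trial care (SPIRIT item 30), calls the intervention routine and well practised. The planned model adjusts for baseline pain, age, sex and procedures, which would absorb part of any prognostic imbalance.

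**Conclusion.** The concern holds as a contradiction in the current text. Section {18b} prescribes a post-randomisation exclusion that the Principles section rules out, and nothing else in the article reconciles the two. This conclusion needs no assumption about rates or prognosis. It should be settled before analysis because it determines the primary analysis population.

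The loss of concealment is conditional: it follows if the slot keeps its arm and the recruiting surgeon knows of the removal. If a fresh draw was meant, that part falls and the intention-to-treat contradiction remains. For {11b}, what is established is only that the exclusion is not limited to requests made before allocation.

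The shift of about 1.05 to 2.35 points and the type I error of about 5.5% to 8% describe an adverse scenario with removals from one arm only, selected on prognosis, and no adjustment. They show what the rule could permit. They do not estimate what will happen, and they do not say which technique would benefit.

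**What to change.** 1. Delete the sentence in {18b} on removal and slot refilling. State instead that every patient whose allocation has been released is followed to 12 months and analysed in the allocated arm, whatever technique was performed, unless the patient withdraws consent to the use of their data.
2. Limit the exclusion in {11b} to requests made before the allocation is released; such patients are not randomised.
3. State that an allocation is never reused and that each new patient receives a newly generated one.
4. Report an adherent-only (per-protocol) analysis as a sensitivity analysis.

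**Cost.** A short protocol amendment, a setting in the randomisation algorithm, and follow-up of a few more patients who are already in the registry with contact at 3, 6 and 12 months. The statistical price is slight dilution if crossover occurs. For example, if 4 of 40 patients in one arm (assumed) received the other technique and its full effect, a true difference of 7.65 would be estimated as 7.65 × (1 − 4/40) = 6.89 points.

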#### Data management {19}

##### Data sources

Patient personal and medical data is routinely collected at the consulting clinics and entered into the practice management systems (Bluechip, MedicalDirector, Australia and Genie, Genie Solutions, Australia). The data is collated with PROMs and organised into the Sydney Orthopaedic Foot and Ankle Research Institute (SOFARI) Registry established within the surgeon’s practice (ACTRN12620000331932), and will form the primary source for patient, clinical, intraoperative and postoperative data for the current trial. Ethical approval for use of the practice registry for research was provided by the New South Wales/Victoria branch of the Ramsay Health Care HREC (HREC approval number 2020-007). Registry data is hosted in a secure, HIPAA-compliant cloud-based database (Google Suite, Google, USA).

##### Data entry

All data collected in this trial will be entered electronically via web-based forms (Google Suite, Google, USA) by either the investigators, research team or participants. The research team will be responsible for the organisation of the data within a HIPAA-compliant database environment (Google Suite, Google, USA) and performing quality assurance checks on the consolidated dataset.

##### Clinic data management

Identifiable data (collected only as necessary for treatment and management of the health services) will be stored permanently on the practice management software, as is standard clinical practice. The data will be stored on a secure server within the consulting rooms, with restricted access.

##### Data linkage processes

Identifiable personal and medical information collected from patients will be stored and kept indefinitely within the database to link patient records to patient information from other sources (e.g. electronic medical records within the practice management systems, clinic notes or radiology records). The research team will access the practice management software in order to conduct quality assurance audits which will involve access to identifiable data, within the environment of the password-protected server.

Web-based forms will be provided to patients to capture validated PROMs using identifiers to link the form responses to the rest of the registry dataset. No identifiable information (name, date of birth, address, contact information) will be included or requested of patients in the forms. Standard operating procedures for data entry will be available to individuals who will require access to the database via a web browser interface to streamline and control data-entry processes. All members with access to the data will have signed a non-disclosure agreement.

Access to the trial data will be password protected. Data will be stored in a HIPAA-compliant environment (Google Suite, Google, USA) prior to further processing locally by the research team. The research team will retain access to the data for the duration of the trial. At the termination of the trial, any study-relevant data will be transferred to the clinic servers and deleted from the research team’s environment. The data gathered will be retained on the existing password-protected servers of the clinic for future reference, publications and potential future studies.

Supplementary information within clinical notes in external databases, such as those at the hospitals where the treatment or surgery is performed or radiology services, will not be integrated directly with the study database. This data will be requested from these systems on an as-needed basis by the surgeons or practice managers, matching patients by name, date of birth and treatment and will be manually transcribed into the practice management system and subsequently into the database.

#### Confidentiality {27}

Confidentiality and privacy of patient information in the trial will be protected through the execution of nondisclosure agreements between all involved parties, prohibiting them from sharing identifiable information externally.

Identifiable trial data is kept electronically on a secure server at the study clinic sites, and de-identified study data will be stored in a secure, HIPAA-compliant online database with access restricted to individual staff members responsible for handling the data.

No identifiable data from the study will be externally shared without consent from the patients. All identifying information such as name, date of birth, email or phone will be removed from any data prior to the transfer of this data to sites not listed in the document. Patient identification numbers will be used as a substitute for identifiable data, and only the investigators will be able to re-identify patients. Patients will not be identified in any publication or presentation resulting from the trial.

All investigators will have unrestricted access to the cleaned data sets. Study data sets will be housed and secured as per the data management procedures outlined in this protocol.

#### Plans for collection, laboratory evaluation and storage of biological specimens for genetic or molecular analysis in this trial/future use {33}

Not applicable; no biological specimens will be collected during this study.

## Statistical methods

### Statistical methods for primary and secondary outcomes {20a}

#### Principles

An analyst blinded to treatment allocation will perform the primary and secondary analyses, by comparing the intervention group to the control group. Data will be analysed following intention-to-treat principles (i.e. participants will be analysed in the group to which they were randomised to). Data normality of baseline characteristics and process measures will be evaluated by visual inspection of histograms. Continuous variables will be presented as means and standard deviations for normally distributed variables: median, minimum, maximum and interquartile range for non-normally distributed variables. Frequencies and percentages will be used to summarise categorical variables. Percentages will be calculated using the number of participants for whom data are available as the denominator. Alpha will be set at 0.05 and effect sizes as described in the sample size calculation will be considered of interest.

#### Data integrity

All data points for the study core dataset will be retrieved electronically, so comparing to original paper records will not be necessary. Data integrity will be defined in the context of this study as completeness, consistency and validity. An error rate of < 3% will be considered acceptable across the total of fields assessed.

Patients who are otherwise lost to follow-up will be included in the analysis under an intention-to-treat framework. Where appropriate, imputation will be used to provide estimates of outcomes for patients lost to follow-up. To mitigate the effects of loss to follow-up on the analysis, the sample size factored in an estimated dropout rate of 10% to ensure adequate power for analyses requiring listwise deletion of missing data.

#### Evaluation of demographics and baseline characteristics

Baseline characteristics will be presented in a table stratified by treatment group. Hypothesis testing of baseline characteristics between the groups will not be performed in accordance with the recommendations of the CONSORT statement [7]. Figure 4 describes the prognostic factors which will be treated as potential confounders of the effect of the intervention and included in the models used to analyse primary and secondary outcomes. These confounders were selected based on the available literature on pain ratings in metatarsalgia [19–23].

**Fig. 4 Fig4:**
[figure not shown]
Directed acyclic graph (DAG) or concept map indicating potential confounders for analysis of the study outcomes

#### Primary outcome analysis

The primary outcome of the trial is postoperative pain at 12 months follow-up represented by the pain subscale of the FAOS. A mixed-effects ANCOVA will be used to test for differences between the groups with the following factors and covariates included in the model:Patient ID (random factors)Baseline FAOS pain subscore (covariate)Age at surgery (covariate)Sex (covariate)Multiple proceduresAdjunct procedures

The overall model fit will be assessed with partial eta^2^ and coefficients (*β*) with 95% confidence limits will describe the strength and direction of relationships between factors and the postoperative FAOS-Pain score. Post hoc comparisons with Dunnett tests (against control) will be used to compare osteotomy groups. Cohen’s *d* will be used to report the effect size of differences between the groups. A Cohen’s *d* exceeding 0.36 will be deemed clinically significant.

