### Objectives {7}

The primary objective of this study is to determine, in patients electing to undergo surgical intervention for propulsive metatarsalgia, whether wedge-cut osteotomy compared to flat-cut Weil (with or without adjunct procedures) is associated with increased pain relief during activities of daily living up to 12 months postoperatively. The secondary objective of this study is to determine whether a lower incidence of procedure-specific complications (floating toe or stiffness) at up to 12 months of follow-up is associated with the wedge-cut procedure, compared to the flat-cut Weil.

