### Outcomes {12}

#### Primary outcome measures

The primary outcome of this trial will be the Foot and Ankle Outcome Score (FAOS) - Pain subscale, collected at up to 12 monthly postoperatively. The FAOS was developed as a foot and ankle-specific PROM assessment analogous to the Knee injury and Osteoarthritis Outcome Score (KOOS), with content validity confirmed with 213 patients with ankle instability [12]. The FAOS consists of 5 subscales: pain, other symptoms, function in daily living (ADL), function in sport and recreation (Sport(Rec)), and foot- and ankle-related quality of life (QOL). Patients rate the questions on a 5-point Likert scale, with 0 representing no symptoms/problems and 4 representing extreme symptoms. The FAOS has been used in patients with lateral ankle instability, Achilles tendonitis and plantar fasciitis, with reliability confirmed in instability patients [12] and responsiveness confirmed in patients with Achilles tendinosis [13] and hallux rigidus [14]. Given the interventions performed in this trial are to treat metatarsalgia, a condition characterised by pain during weight-bearing activity, particularly noticeable during the push-off phase of the gait cycle, the pain subscale of the FAOS Questionnaire was selected as the most clinically relevant patient-reported measure for the purposes of measuring the primary outcome of this trial. One study reported an MCID of 15.3 points (95% confidence interval 10–20.6) [15], with a difference between groups equal to half this (7.7) deemed sufficient to guide future decision-making with respect to technique selection. For analysis purposes, a mixed-effects model will be used, which will aggregate scores from all responders and report mean and standard deviation (SD) associated with different combinations of model predictors, such as intervention group, sex and adjunct procedures.

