### Sample size {14}

The sample size required for the primary outcome was established to provide adequate power to detect half an MCID difference (15.3/2) in the FAOS Pain score between the control flat-cut Weil and experimental wedge-cut groups, with an average estimated baseline standard deviation of 20.8. The MCID and baseline SD were derived from a previous study [15], and 0.5MCID was determined to be a clinically important effect that would influence future clinical decision-making regarding technique selection. A mixed-effects model (analysis of covariance (ANCOVA)) was selected as the most appropriate to answer the question posed, with power (*β*) at 0.9 and *α* of 0.05, with an allowance for a dropout rate of 10%. The required sample size was determined using GPower [18] to be *N* = 80 patients, with patient age at surgery, sex, body mass index, single/multiple procedures and adjunct procedures included as model covariates.

The sample size required for the secondary outcome was established to provide adequate power to detect a 15% reduction in complication incidence from a baseline of 60% incidence. The reduction in incidence was deemed to be the minimal amount of improvement that would influence future decision-making regarding technique selection in this patient population. A one-sided test within a logistic regression model was selected within GPower, with the *R*^2^ for other predictors in the model (patient age at surgery, sex, body mass index, single/multiple procedures and adjunct procedures) set to 0.1. The required sample size was determined to be *N* = 123 procedures.

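### The primary mixed model has a random patient factor but no visit or group-by-visit term, so it does not match the stated 12-month endpoint

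*Protocol article*

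**What the plan says.** The Primary outcome analysis section fixes the endpoint: "The primary outcome of the trial is postoperative pain at 12 months follow-up represented by the pain subscale of the FAOS". It then gives the model: "A mixed-effects ANCOVA will be used to test for differences between the groups with the following factors and covariates included in the model". The list reads "Patient ID (random factors)Baseline FAOS pain subscore (covariate)Age at surgery (covariate)Sex (covariate)Multiple proceduresAdjunct procedures". Neither visit nor an interaction of group with visit appears in it, or anywhere else in the article.

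Other sections use a looser time frame. Under Objectives {7} the question is whether the wedge cut "is associated with increased pain relief during activities of daily living up to 12 months postoperatively". Under Primary outcome measures the subscale is "collected at up to 12 monthly postoperatively", and the mixed model is described as one "which will aggregate scores from all responders and report mean and standard deviation (SD) associated with different combinations of model predictors". Section {18b} says of enrolled patients that "they will be contacted at 3, 6 and 12 months postoperatively for PROMs follow-up data collection". No section says which of these visits enter the primary model.

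The covariates also differ between sections. Sample size {14} names age, sex, "body mass index, single/multiple procedures and adjunct procedures included as model covariates", without the baseline pain score. The analysis section has the baseline pain score and no body mass index.

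**The concern.** A random patient factor has a purpose only if a patient contributes more than one outcome row. The endpoint as stated gives one row per patient. The collection schedule gives up to three, but the listed model has no term that would isolate the 12-month visit. The printed endpoint and the printed model therefore do not fit each other, and the article does not say which of the two should give way.

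The two ways out answer different questions. A difference at 12 months and an average difference over 3 to 12 months are separate claims about the wedge cut. The analysis section supports the first, and the wording of the objective leans towards the second. If this stays open until the data are in, the primary result could depend on a choice made late.

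**Working it through.** The plan gives no figure of its own for this point, and the check does not depend on the sample size calculation. Each reading of the model is taken in turn.

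**Inputs from the protocol article.** Endpoint at 12 months and model terms (Primary outcome analysis); scores at 3, 6 and 12 months ({18b}); target difference 15.3/2 = 7.65 points, 80 patients, 10% dropout (Sample size {14}).

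**Assumed inputs, not in the article.** The effects at 3 and 6 months and the variance components used below.

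**Reading 1: one 12-month score per patient.** Write the score as y_i = x_i'β + u_i + e_i, with patient variance σ_u² and residual variance σ_e². Each patient appears once, so the likelihood contains only the sum V = σ_u² + σ_e²:

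log L = −½ [ n log(2πV) + r'r / V ], with r the vector of residuals.

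This was evaluated on one simulated data set with n = 80 × 0.9 = 72 and V = 18² = 324:

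| σ_u² | σ_e² | log L |
|---|---|---|
| 0 | 324 | −308.386 |
| 100 | 224 | −308.386 |
| 200 | 124 | −308.386 |
| 300 | 24 | −308.386 |

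The likelihood is flat, so the split cannot be estimated. The estimate of β does not depend on the split, so the group coefficient is that of an ordinary ANCOVA.

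**Reading 2: three scores per patient, no visit terms.** With complete data, the random-intercept model gives the same group coefficient as an ANCOVA on patient means. Its target is

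δ_avg = (δ_3 + δ_6 + δ_12) / 3.

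- Constant effect: (7.65 + 7.65 + 7.65)/3 = 7.65.
- Growing effect: (0 + 3.825 + 7.65)/3 = 3.825.
- Fading effect: (15.3 + 11.475 + 7.65)/3 = 11.475.

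A simulation of 20,000 patients per scenario (assumed between-patient SD 15, residual SD 14 at each visit) agrees within simulation error:

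| Assumed effect at 3 / 6 / 12 months | Averaged model | 12-month ANCOVA |
|---|---|---|
| 7.65 / 7.65 / 7.65 | 8.05 | 8.04 |
| 0 / 3.8 / 7.65 | 3.86 | 7.60 |
| 15.3 / 11.5 / 7.65 | 11.66 | 7.77 |

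The "averaged model" column is the ANCOVA on patient means. Direct mixed-model fits to 600 of these patients were noisier. Without visit terms against the 12-month contrast from a group-by-visit model, they gave 9.11 against 8.69 (constant), 5.03 against 7.83 (growing) and 11.35 against 9.16 (fading).

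**Reading 3: several procedures per patient.** The random factor might be meant for patients with more than one osteotomy. Sample size {14} and Recruitment {15} count patients (80) for the primary outcome and procedures (123) only for the secondary. No pain score per foot or per procedure is described. Repeating one patient score over procedures would leave no variation within a patient.

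**Missing 12-month scores.** The planned dropout is 10% × 80 = 8 patients. Some of them may have a 3- or 6-month score.

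**The case against.** The strongest reply is that the analysis section does fix 12 months. The contacts at 3, 6 and 12 months are described as registry procedure under retention, not as model input, and the sentence on aggregating scores refers to responders, not visits. On that reading the model still gives the adjusted 12-month difference, with one superfluous term. This stands as far as the estimate goes. A reader might infer that the listed model cannot deliver the 12-month contrast at all, and Reading 1 shows that this is wrong. What remains is that the specified model has a component that the data cannot support.

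A second reply is that the list is plainly incomplete. It omits even the intervention group, the article condenses a fuller protocol, and the statistical code is to be posted. A missing visit term is therefore weak evidence that none is intended. This is fair, but the gap for group is filled elsewhere in the article: the text says that groups are tested, and Primary outcome measures names group as a predictor. Nothing fills the gap for visit. The point is a mismatch between two printed statements, not the absence of detail.

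Third, a reader might infer that patients without a 12-month score contribute nothing. Section {20c} plans multiple imputation when forms are not returned, and the Data integrity section keeps patients lost to follow-up in the analysis, so that inference fails. The imputation variables are not stated, however, and the Data integrity section also anticipates analyses with listwise deletion.

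Fourth, Figure 4 is not shown and may list body mass index among the confounders. That could explain one half of the covariate conflict, but the two printed lists still differ.

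**Conclusion.** The point holds as a mismatch between the stated endpoint and the stated model, and it should be corrected. With one row per patient, the harm is a redundant random factor or a failed fit, and the group estimate is intact. With three rows, the primary coefficient has a different target. Its distance from the 12-month difference depends on how the effect changes over time, which the article neither assumes nor tests.

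A reader might infer a fixed underestimate from a growing effect. The documents do not support any particular size or direction: the gap is zero under a constant effect, about 3.7 points too low in the growing scenario (7.60 − 3.86) and about 3.9 points too high in the fading one (11.66 − 7.77). These trajectories are assumptions. The flat likelihood in Reading 1 is exact. The simple average in Reading 2 holds for complete data.

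**What to change.** Specify a repeated-measures mixed model on the 3-, 6- and 12-month FAOS-Pain scores, one row per patient and visit. Its terms would be group, visit, group-by-visit, baseline pain score, baseline-by-visit and the prespecified covariates. Name the group difference at 12 months as the primary test. This model also uses earlier scores directly for patients missing at 12 months, up to about 8 of 80.

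The minimum alternative is an ANCOVA of the 12-month score without the patient random factor. It removes the contradiction but leaves missing scores to the planned imputation, whose variables should then be stated.

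In either case:
- Say at 12 months in Objectives {7} and Primary outcome measures.
- Give one covariate list in Sample size {14} and Primary outcome analysis, settling body mass index and the baseline pain score.
- Define multiple and adjunct procedure status as planned before the allocation code is released. The surgeon receives the code on the day of surgery and is not blinded, so status recorded afterwards could depend on arm.

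The cost is analysis wording and code. The 3- and 6-month scores are already in the collection schedule.
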